### Data Collection Tools

BP will be measured using validated electronic arm-cuff devices following standardized procedures: 3 measurements at 1- to 2-minute intervals after 5 minutes of rest, recording systolic and diastolic pressure in both arms following the European Society of Hypertension guidelines. Mediators document results immediately on structured forms and provide participants with referral slips if indicated. Sociodemographic, anthropometric, and medical history data will be collected using a paper-based questionnaire estimated to require 30 minutes per participant. The questionnaire included demographic data (age, sex, country of birth, languages spoken, and duration of residence), medical history (previous hypertension diagnosis, current medications, and cardiovascular events), health care access (insurance status, usual source of care, and barriers to access), and lifestyle factors (smoking, alcohol consumption, physical activity, and dietary habits). For participants with suspected hypertension, a standardized 3-month phone follow-up will be performed using a semistructured script to capture referral completion and treatment adherence. Administrative data on hospitalizations, diagnoses, and prescriptions will be accessed from the regional PMSI [32] and national health insurance databases. PMSI is a French hospital discharge database that compiles standardized clinical and administrative information on all inpatient stays in both public and private hospitals. It includes data such as patient demographics, diagnoses, medical procedures, and length of hospital stay. This system enables the construction of patient cohorts based on variables such as age, sex, comorbidities, and disease severity. Data are routinely collected from health care facilities, ensuring comprehensive population coverage and minimizing selection bias. Its use is governed by strict ethical and data protection regulations. No biological samples will be collected.

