McNemar test is a nonparametric method used to analyze paired nominal data, particularly in situations where the same participants are measured at 2 time points, such as before and after an intervention. It is designed to detect changes in proportions by focusing exclusively on discordant pairs—cases where the response changed between the 2 time points—while ignoring concordant pairs in which no change occurred. This makes it especially suitable for evaluating shifts in binary outcomes within matched or repeated-measures designs, where observations are not independent.

Trends in antihypertensive prescription volumes, obtained from health insurance reimbursement data, will also be evaluated over the preintervention and postintervention periods using ITS models to assess the effect of the intervention at the population level.

Missing data will be systematically evaluated for all variables. For descriptive analyses, the number of participants with available data will be reported. For analytical purposes, the mechanism of missingness will be assessed (eg, missing completely at random, missing at random, or missing not at random). If data are found to be missing at random, multiple imputation via chained equations (MICE) [36] will be considered for inclusion in multivariable and ITS analyses. MICE is a flexible and iterative method for handling missing data by creating multiple complete datasets. It works by modeling each variable with missing values conditionally on all other variables in the dataset, using appropriate regression models depending on the type of variable (eg, linear for continuous variables and logistic for binary variables). This chained approach allows the preservation of complex relationships among variables and accommodates different data types, improving the validity and efficiency of statistical inferences drawn from incomplete data.

As a sensitivity check, complete-case analyses will also be performed. The influence of missing data on primary and secondary outcomes will be explicitly reported.

Sample size calculations were conducted using the following two complementary approaches.

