However, several limitations must be acknowledged. The quasi-experimental design without randomization means that temporal confounders (such as concurrent public health campaigns, changes in health care access, or secular trends in treatment patterns) may influence outcomes independently of the intervention. Although we will attempt to control for these through comparison with nonintervention regions in French Guiana, unmeasured confounding remains possible. Reliance on administrative datasets, while ensuring comprehensive capture, may be subject to coding inaccuracies or changes in diagnostic practices over time. However, the use of validated *International Statistical Classification of Diseases and Related Health Problems, 10th revision* (ICD-10) codes for stroke diagnosis and the consistency of PMSI reporting requirements over the study period minimize this concern. Implementation heterogeneity across neighborhoods (varying in size, accessibility, and population composition) may introduce variability in intervention dose and reach. We will document coverage rates by neighborhood and explore heterogeneity in subgroup analyses, but differences in how intensively the intervention was implemented across neighborhoods may influence the results. For secondary outcomes assessed through participant questionnaires and telephone follow-up (eg, referral adherence, treatment initiation, and satisfaction), self-reported data may be subject to social desirability and recall biases. Additionally, loss to follow-up during the 3-month telephone interviews may affect internal validity for these secondary end points, although we plan to use multiple imputation techniques and will report sensitivity analyses restricted to complete cases. These limitations, however, do not affect the primary outcome analysis, which relies exclusively on objective administrative data. Finally, the exclusion of individuals under legal protection (eg, guardianship) is required by French research regulations but may reduce generalizability to populations with severe cognitive impairment or psychiatric conditions, groups that may also experience an elevated risk of cardiovascular disease. Despite these limitations, this study addresses a critical gap in stroke prevention research in underserved populations and will provide valuable evidence on the effectiveness and scalability of community-based hypertension screening in resource-limited settings.

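### Imputation depends on a missing-at-random finding that data cannot supply, and the one named check, complete-case, can share its bias for the 3-month telephone endpoints

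*Protocol article*

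**What the plan says.** The missing-data text is in the protocol article, Methods, Statistical Analysis. It says that "the mechanism of missingness will be assessed (eg, missing completely at random, missing at random, or missing not at random". The next sentence sets the condition for imputation: "If data are found to be missing at random, multiple imputation via chained equations (MICE". Even then the method is only an option to be weighed, and it is attached to multivariable models and to ITS. Two further commitments follow. The first is a check: "As a sensitivity check, complete-case analyses will also be performed". The second concerns reporting: "The influence of missing data on primary and secondary outcomes will be explicitly reported". No action is given for data judged MNAR.

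Referral completion and treatment adherence come from the telephone call. Under Data Collection Tools, for participants with suspected hypertension, "a standardized 3-month phone follow-up will be performed using a semistructured script to capture referral completion and treatment adherence". Someone who is not reached therefore has no value for these outcomes.

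Strengths and Limitations returns to the subject. It concedes that "loss to follow-up during the 3-month telephone interviews may affect internal validity for these secondary end points" and answers that "we plan to use multiple imputation techniques and will report sensitivity analyses restricted to complete cases".

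**The concern.** There are three linked problems.

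- **The trigger cannot be evaluated.** MAR and MNAR differ in whether missingness depends on the unseen value once the observed data are taken into account. No examination of the observed data settles that.
- **Two sections disagree about where imputation applies.** Statistical Analysis attaches it, conditionally, to multivariable and ITS analyses. Strengths and Limitations plans it, without that condition, for the telephone endpoints. Statistical Analysis assigns participant-level questionnaire data, including adherence indicators and treatment uptake, to McNemar or Wilcoxon signed-rank tests, which are neither multivariable nor ITS.
- **The named check may fail in the same way as the method it checks.** If people who did not see a clinician or start treatment are harder to reach by telephone, imputation under MAR and complete-case analysis both extend the experience of those reached to those who were not.

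Referral adherence and treatment initiation are at stake. The Discussion (Comparison to Prior Work) presents both as points where this programme may do better than earlier ones.

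**Working it through.** The article states no figure for telephone loss, referral completion or treatment initiation, so there is nothing to reproduce. The inputs below are assumptions, shown as ranges.

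**1. Can the trigger be evaluated?** Baseline characteristics are known for reached and unreached participants. Comparing them can contradict missing completely at random. MAR requires more: among people with the same baseline data, being reached must not depend on whether referral was completed. Completion is unseen for the unreached, so the data cannot test this.

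**2. How far could the reported figure be from the truth?** Let m be the proportion unreached, p the completion among those reached and u the completion among those unreached.

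- True completion = (1 − m) × p + m × u
- Overstatement, if p is reported for everyone = m × (p − u)

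With p = 70% (assumed):

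| Unreached (m) | Unreached complete half as often (u = 35%) | None of the unreached complete (u = 0) |
|---|---|---|
| 20% | 0.80 × 0.70 + 0.20 × 0.35 = 63% | 0.80 × 0.70 = 56% |
| 40% | 0.60 × 0.70 + 0.40 × 0.35 = 56% | 0.60 × 0.70 = 42% |

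The overstatement is 7 and 14 points in the middle column, and 14 and 28 points in the extreme one. With p = 50% the corresponding gaps are 5 and 10 points, and 10 and 20 points. If the unreached complete as often as the reached, the gap is zero.

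**3. Would complete-case analysis expose the problem?** This was simulated with 200,000 participants, all inputs assumed. Completion depended on insurance status and age. Being reached depended on insurance status alone (the MAR case) or on insurance status and completion itself (the MNAR case, log-odds coefficient 1.0). Imputation used 20 draws from a logistic model containing insurance status and age.

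| Case | Missing | Truth | Imputation under MAR | Complete-case |
|---|---|---|---|---|
| MAR | 35% | 60.7% | 60.7% | 61.1% |
| MNAR | 24% | 60.7% | 66.4% | 66.8% |

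In the MNAR case the two planned methods agree within 0.5 points, and both are about 6 points too high. Their agreement says nothing about the error.

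**4. Would a delta-adjusted analysis help?** In the same MNAR case, the log-odds of completion for the unreached were shifted by 0, −0.5, −1.0 and −1.5. The results are 66.5%, 63.6%, 60.6% and 57.9%, a range that includes the true 60.7%.

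**5. ITS.** An aggregated monthly count contains no missing participant value for chained equations to fill. The individual records behind the counts may, for example in the coverage markers that Statistical Analysis uses for stratification when available.

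**The case against.** The strongest reply is that Strengths and Limitations already plans imputation for the telephone endpoints without the faulty condition, and that an analysis plan not shown here may hold an MNAR analysis. The first part stands: imputation of these endpoints is not absent, and what remains is a conflict between two sections. The second is possible, but it does not rescue the stated rule. A further document could replace the condition but could not make it testable. The sensitivity check is also named in both places, and in both it is complete-case alone.

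Several stronger readings are tempting, and the documents do not support them.

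- **That referral adherence will be overstated.** Nothing in the article links non-contact to non-completion. Intervention or Treatment mentions population mobility, which could cause non-contact for other reasons. Baseline insurance and access data could also move the imputed figure away from the complete-case one.
- **That the bias would reverse a comparison with 60%.** That figure could be inferred from the Discussion's remark that more than 40% of referred patients in prior studies did not access follow-up care. The remark makes 60% only a ceiling, and no planned analysis tests against it.
- **That nothing planned would show the problem.** The numbers with available data and the influence of missing data are to be reported. Those counts would let a reader work out the extreme bound, though no tool beyond imputation and complete-case is named.
- **That imputation has no place in ITS work.** Imputing a record-level marker before aggregation can be legitimate.

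**Conclusion.** The concern holds in a limited form. The condition for imputation cannot be carried out as written, the two sections differ on where imputation applies, and agreement between imputation and complete-case analysis would not rule out overstated referral adherence or treatment initiation.

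The size cannot be fixed from the article. The 7 to 14 point gap rests on assumed values of 70% completion among those reached, 20% to 40% unreached, and half the completion rate among the unreached. The 14 to 28 point gap is an extreme bound. The direction is plausible but not shown.

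Only secondary endpoints from the telephone call are concerned. The primary stroke outcome comes from hospital discharge data and is unaffected. The point should be corrected, but it does not threaten the main conclusion.

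**What to change.** 1. State MAR as an assumption, not as something to be found, and make imputation by chained equations the main analysis for the 3-month telephone endpoints. Bring Statistical Analysis into line with Strengths and Limitations on this.
2. Keep complete-case analysis, and add a delta-adjusted (MNAR) sensitivity analysis for referral completion and treatment initiation. Run it from no shift to the bound at which everyone not reached is counted as referral not completed or treatment not started. Report it next to the number reached.
3. In ITS work, limit imputation to record-level variables before aggregation. Do not apply it to the aggregated counts.

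The cost is a few extra model runs, a few sentences of analysis text and a wider reported range for these endpoints. No new data are needed.

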### Intervention or Treatment

The intervention will consist of a comprehensive, community-delivered hypertension screening and education program. It will be implemented by 12 trained health mediators organized into 3 teams of 3 to 4 mediators each. The protocol stipulates that each mediator can screen approximately 10 people per day, representing a target of 2000 adults per month. These mediators, certified through a university-level diploma in health mediation or with equivalent field experience, will engage directly with residents in all precarious neighborhoods within the CACL. Each neighborhood will receive at least 1 intervention visit during the 24-month intervention period. The number of visits per neighborhood will be determined based on population size and accessibility. The goal is comprehensive coverage of an estimated population of 50,000 adults in the target neighborhoods.

To maximize reach, each visit will last 1 to 2 days, with mediators establishing fixed screening posts and conducting door-to-door outreach. The quantification of coverage will not be based solely on the number of individuals screened but on the number of neighborhoods fully investigated by the mediators. The intervention will be considered complete for a neighborhood when the minimum number of planned visits has been conducted, when mediators have systematically covered all streets or sectors through door-to-door approaches, or when repeated visits yield diminishing returns.

Given population mobility and the informal nature of precarious settlements, we acknowledge that precise denominator estimation is challenging. Mediators will set up mobile stations or conduct home visits to measure BP triadically according to European guidelines, provide personalized health education focused on hypertension and lifestyle modification, assess health insurance coverage, and guide participants with elevated BP to appropriate health care professionals or social services (eg, general practitioners or the PASS unit). Follow-up will include a structured telephone call 3 months later to assess completion of the medical referral process.

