### Outcome Measures

The primary outcome will be the change in the incidence of stroke comparing the 5-year preintervention period with the 2-year period following the start of the intervention, as recorded in the Programme de Médicalisation des Systèmes d’Information (PMSI) database. Secondary outcomes will include changes in incidence of ACS [28], TIA [29], PAD [30], aneurysm, and ESRD [31] (*insuffisance rénale terminale* [IRT]), as well as all-cause cardiovascular mortality within 1, 2, and 3 years after the intervention. ACS refers to a spectrum of urgent cardiac conditions caused by a sudden reduction in blood flow to the heart muscle due to a partial or complete blockage of the coronary arteries. This group of conditions includes unstable angina and non–ST-elevation myocardial infarction (NSTEMI), both of which require prompt diagnosis and individualized treatment strategies to prevent further cardiac damage and improve patient outcomes.

ESRD represents the final and most advanced stage of chronic kidney disease, defined by a severely reduced GFR of less than 15 mL/min/1.73 m^2^. At this stage, patients require kidney replacement therapy, which includes either long-term dialysis or kidney transplantation. ESRD is a chronic condition that typically arises in the context of long-standing comorbidities, notably hypertension.

PAD is a circulatory condition characterized by the narrowing or blockage of peripheral arteries, most commonly in the lower limbs, due to the buildup of atherosclerotic plaques. This reduced blood flow can lead to symptoms such as leg pain during walking (claudication), numbness, or even tissue damage in severe cases. Importantly, PAD is not confined to the extremities; it reflects a systemic atherosclerotic process that affects multiple vascular beds. As such, PAD serves as a clinical marker for widespread vascular dysfunction and is strongly associated with an elevated risk of major cardiovascular events, including myocardial infarction and stroke.

Additional secondary end points will assess participants’ adherence to medical referrals, satisfaction with the program, the number of BP screenings completed, the number of new or rediagnosed hypertensive cases, and changes in antihypertensive prescription patterns using health insurance data. Outcome assessments will be based solely on administrative records and structured questionnaires, minimizing subjectivity and measurement variability.

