### Statistical Analysis

Statistical analyses will be conducted using Stata (version 19; StataCorp). Continuous variables will be described using means and SDs when normally distributed; for skewed distributions, medians and IQR will be reported. Normality will be assessed using visual inspection of histograms and quantile-quantile plots and confirmed with the Shapiro-Wilk test.

Comparisons of continuous variables between groups (eg, before vs after the intervention and intervention vs control regions) will be performed using the Student *t* test or the Mann-Whitney *U* test, as appropriate. The Student *t* test is a statistical method used to determine whether the means of 2 independent groups are significantly different from each other. It assumes that the data in each group are approximately normally distributed and that the variances are equal or similar.

Categorical variables will be summarized as absolute frequencies and percentages. Between-group comparisons will be conducted using chi-square tests or Fisher exact tests.

All statistical comparisons will be 2-sided, and results will be considered statistically significant if *P*<.05. Corresponding 95% CIs will be reported for all estimated parameters.

The primary outcome analysis will assess the difference in stroke incidence before and after the 2-year intervention period among residents of precarious neighborhoods within the CACL of French Guiana. Stroke incidence, derived from PMSI hospitalization data, will be compared across the 2 periods using the chi-square test. To evaluate temporal trends and detect structural breaks attributable to the intervention, segmented regression of interrupted time series (ITS) [33] data will be applied. The ITS model will estimate the immediate change in level and the change in slope after the intervention, while adjusting for autocorrelation and seasonality as necessary based on model diagnostics (Figure 3).

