The primary approach uses the chi-square test; approximately 350 patients with stroke are admitted annually to the Centre Hospitalier de Cayenne, with 68% (n≈238) occurring among socioeconomically precarious patients. Assuming the intervention leads to a 30% reduction in stroke incidence within this population—consistent with previous international interventions—a postintervention count of approximately 167 strokes per year (a reduction from 238) is anticipated. To detect this effect with 90% power at a 5% significance level (α=.05) using a 2-sided chi-square test comparing proportions before and after the intervention, a minimum of 367 cumulative postintervention stroke cases over a 2-year period is required.

Second, a segmented regression (ITS) analysis will be used to complement the chi-square test by examining both immediate level changes and slope changes after the intervention. On the basis of 60 monthly preintervention observations (5 years) and 24 monthly postintervention observations (2 years), and assuming autocorrelation (ρ=0.3-0.5) typical of health administrative data, this design provides adequate power (>80%) to detect a change in slope corresponding to a 20% to 30% reduction in incidence, assuming a baseline coefficient of variation of 15% to 20% in monthly stroke counts.

The chi-square test provides a straightforward test of the primary hypothesis, while ITS analysis accounts for underlying temporal trends and potential confounders, offering a more nuanced understanding of intervention effects. Both analyses will be reported, with ITS serving as the primary confirmatory analysis and the chi-square test as a sensitivity check.

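### The before/after chi-square on proportions has no person-time basis for windows of 5 and 2 years; it should be an incidence rate ratio, and the first sample-size approach should be restated on 5:2 exposure

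*Protocol article*

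**What the plan says.** All places are in the Methods of the protocol article.

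- **Outcome Measures** defines the primary outcome as a change in stroke incidence, "comparing the 5-year preintervention period with the 2-year period following the start of the intervention".
- **Statistical Analysis** gives the test: "Stroke incidence, derived from PMSI hospitalization data, will be compared across the 2 periods using the chi-square test".
- **Statistical Analysis, sample-size paragraphs** describe the same test and the number of events it needs: "using a 2-sided chi-square test comparing proportions before and after the intervention, a minimum of 367 cumulative postintervention stroke cases over a 2-year period". The inputs are about 350 strokes a year, "with 68% (n≈238) occurring among socioeconomically precarious patients", and a 30% reduction to about 167 a year, at 90% power and two-sided 5% significance.
- **The end of those paragraphs** makes the ITS the primary confirmatory analysis and the chi-square a sensitivity check, with both to be reported. It also describes the chi-square as a straightforward test of the primary hypothesis.
- **Intervention or Treatment** contains the only population size, an estimated 50,000 adults given as a coverage goal. On population size it adds: "we acknowledge that precise denominator estimation is challenging".

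**The concern.** A chi-square on proportions takes events over persons and carries no exposure time. With windows of 5 and 2 years, the result depends on what goes into the numerator and denominator, and the article states neither. It speaks of incidence in one place and of proportions in another, and it moves between annual and cumulative counts within one sample-size paragraph.

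At stake is whether the sensitivity check can do its job. Depending on an unstated choice, it could agree with the ITS, show a large artefactual fall, or give an interval that is too wide. If the choice is left open until the counts are seen, agreement or disagreement with the ITS says little. The first sample-size approach has the same gap.

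**Working it through.** **Inputs.** From the article: 238 strokes a year before the intervention (350 × 0.68), a 30% reduction, windows of 5 and 2 years, monthly coefficient of variation (CV) 15% to 20%, and autocorrelation ρ of 0.3 to 0.5. Assumptions: N = 50,000 adults as the population in both windows (the article gives this only as a coverage goal), and independent Poisson counts unless stated otherwise.

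Expected counts are 5 × 238 = 1190 before. After, they are 2 × 238 = 476 with no effect, or 476 × 0.7 = 333 with the planned effect.

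**The plan's own figure.** The usual two-proportion formula (pooled variance, no continuity correction, two-sided 5%, 90% power) was applied to 238/50,000 versus 166.6/50,000.

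- Equal exposure requires 41,526 person-years per period, so 41,526 × 166.6/50,000 ≈ 138 strokes after the intervention.
- Exposure of 5:2 requires 73,716 person-years before and 29,486 after, so 29,486 × 166.6/50,000 ≈ 98 strokes after the intervention.

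Neither gives 367, and no variant tried gave it as a postintervention count at the stated power and significance level. The exposure basis therefore cannot be recovered from the sizing.

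**Reading 1: person-years.** With no effect, 1190/250,000 versus 476/100,000 gives a ratio of 1.00, and the simulated type I error is 5.0%. With the planned effect, 1190 versus 333 gives a ratio of 0.70. The SE of the log ratio is √(1/1190 + 1/333.2) = 0.062, so the 95% CI is 0.62 to 0.79. This reading is valid.

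**Reading 2: cumulative counts over a fixed headcount.** With no effect, 1190/50,000 = 2.38% versus 476/50,000 = 0.95%. The ratio is 0.40, an apparent fall of 60%. The chi-square is 311 (309 to 319 for N from 100,000 down to 20,000), and the null was rejected in every simulated trial.

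**Reading 3: annualised counts over a fixed headcount.** The 1190 baseline strokes enter as 238, and the 2-year count enters as one year's count.

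| True effect | SE on full counts | SE on annualised counts | Ratio |
|---|---|---|---|
| None | √(1/1190 + 1/476) = 0.0542 | √(2/238) = 0.0917 | 1.69 |
| 30% reduction | 0.0620 | √(1/238 + 1/166.6) = 0.1010 | 1.63 |

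At a 30% reduction the 95% CI becomes 0.57 to 0.85 instead of 0.62 to 0.79. Simulated type I error is about 0.1%. Simulated power is 99.7% at a 30% reduction. At a 20% reduction it is about 72% to 73%, against 97% with person-years.

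**Effect of the plan's own CV and autocorrelation.** The SE of the log ratio under no effect is approximately CV × √((1+ρ)/(1−ρ)) × √(1/60 + 1/24).

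- At CV 15%, ρ 0.3, it is 0.049. At CV 20%, ρ 0.5, it is 0.084.
- The annualised SE of 0.0917 is then 1.86 to 1.10 times the correct one. With Poisson variation (monthly CV 22.5%) and ρ 0.5 the ratio is 0.98.
- The plain Poisson SE of 0.0542 would give a type I error of about 3% to 20% over the same range. Quasi-Poisson scaling leaves serial correlation untouched and gives about 15% (ρ 0.3) to 26% (ρ 0.5).

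**Population change.** The window midpoints are 2.5 + 1 = 3.5 years apart. Assumed growth of 1%, 2%, 3% or 4% a year (not in the article) multiplies a fixed-denominator ratio by (1+g)^3.5 = 1.04, 1.07, 1.11 or 1.15. A true 30% reduction would then appear as 28%, 25%, 22% or 20%.

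**The case against.** The strongest reply is that the article says incidence, both in the outcome definition and where the chi-square is introduced. Person-years fit that word, and on that reading the test is sound. No passage makes the 50,000 adults the stroke denominator or says that cumulative counts will be used. The assumed effect, 238 to 167, is on an annual scale. A reader might infer that the plan will report a spurious 60% fall; the text does not support that, because the figure belongs to one possible reading.

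A reader might also infer that the confirmatory result is compromised. It is not: the ITS works on 60 and 24 monthly observations, and unequal window lengths do not bias it. Nor is the annualised reading a serious loss of power. Its error is conservative, and at the planned effect almost nothing is lost.

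All of this stands. It is also true that a condensed article may leave the source of person-time to an analysis plan. It does not remove the point, because the article goes beyond leaving a detail open. It names a test on proportions, which does not suit unequal exposure, and bases its first sample-size approach on that test without an exposure basis.

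**Conclusion.** The concern holds in limited form. The named test does not fit windows of 5 and 2 years unless its denominator is person-time, and the article does not say that it is. On the literal headcount readings, the result is either a 60% apparent fall under no effect or a standard error 1.6 to 1.7 times too wide. Those sizes rest on 238 strokes a year and independent Poisson counts; the chi-square value also assumes 50,000 adults in both windows. Under the plan's own CV and autocorrelation, the excess width under no effect ranges from 1.86 down to 1.10 times and is below the Poisson value of 1.69 in most of that range.

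The point reaches the reported sensitivity check and the first sample-size approach only. It should be settled before the outcome analysis, but it does not threaten the confirmatory analysis. That 367 also exceeds the 333 strokes expected under the assumed reduction is a separate matter.

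**What to change.** In Statistical Analysis, including its sample-size paragraphs:

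1. Replace the chi-square on proportions with an incidence rate ratio and 95% CI from a count model of monthly strokes, with a period term and an offset of log person-time. Use standard errors that allow for overdispersion and autocorrelation, for example Newey-West. Plain Poisson or quasi-Poisson errors do not cover the assumed ρ of 0.3 to 0.5.
2. State how the adult population is estimated for each year, and derive monthly person-time from it.
3. Repeat the rate ratio over a stated range of annual population growth, because the article concedes that the denominator is uncertain.
4. Restate the first sample-size approach as a rate-ratio calculation with 5 and 2 years of exposure.

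The cost is revised wording, a restated calculation and one extra sensitivity run. The ITS already requires monthly counts, and no new participant data are needed. The small downside is that the estimate depends on the population figures used, which the sensitivity range makes visible.
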